#### Methods in analysis to handle protocol nonadherence and any statistical methods to handle missing data {20c}

All available data will be used in the models. Screening, recruitment, consent forms, withdrawal, amendments to protocol and occurrence of protocol deviations, and serious adverse events will be monitored by A + Science. In case of detected irregularities, additional on-site monitor visits will be scheduled.

### Plans to give access to the full protocol, participant-level data, and statistical code {31c}

Participants will provide consent to share deidentified information for future research. Deidentified datasets can be obtained from the principal investigator upon reasonable request and under formal data transfer agreements to facilitate additional research. Moreover, transparency and reproducibility will be upheld by making the study protocol and the statistical code utilized accessible to interested parties.

### Oversight and monitoring

#### Composition of the coordinating center and trial steering committee {5d}

The team responsible for recruitment and administrative task of the daily tasks in the trial meets weekly. The group consists of the principal investigator, project leader, and staff responsible for recruitment activities. A + Science will monitor the trial, such as the presence of signed informed consent, documentation of inclusion/exclusion criteria, and randomization for each participant, and compare the digital data with source data. A minimum of 14 visits to the study site are planned during the study period.

#### Composition of the data monitoring committee, its role and reporting structure {21a}

The intervention researched in the trial is of low risk, and the Human Research Ethics Committee does not require a Data Monitoring Committee.

### Adverse event reporting and harms {22}

Therapists and assessors are instructed to immediately notify the principal investigator study team should they be concerned that a participant has caused, or is likely to cause, significant harm to themselves or others and complete a risk assessment. If a participant scores more than 2 points on the self-reported PHQ-9 item 9, which assesses the presence and duration of suicidal ideation, they are identified through an alert flag in the digital platform and subsequently contacted by a clinician via phone.

The occurrence of undesirable treatment effects can be reported by the participant at any point through the study period by alerting the designated therapist or assessor or contacting the study personnel. The therapist and assessor will be instructed to ask follow-up questions about the intensity, duration, and characteristics of the adverse event. All reported adverse events will be classified as mild, moderate, or severe and handled according to the clinics’ routines, reported to A + Science and described on a case-by-case basis. The event will be classified as serious if it is life-threatening, results in death or persistent/significant disability/incapacity, requires hospitalization or its prolongation, or is considered medically significant by the principal investigator. The NEQ will be used posttreatment and follow-ups to capture potential adverse effects in a structural way. Previous studies that have investigated intensive prolonged exposure have not detected any serious adverse events. All participants will be closely monitored during the study, and additional treatment will be provided in case of an unlikely severe deterioration.

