### Assignment of interventions: blinding

#### Who will be blinded {17a}

The therapists and the participants in the trial cannot be blinded to treatment allocation due to the complex nature of the treatment, but group allocation will be masked to the assessors up to completion of the 12-month follow-up. Participants will receive explicit instructions not to discuss their treatment allocation with the assessor. If a participant still unintentionally discloses their treatment allocation, another blind assessor will reassess the diagnosis and symptom severity using recordings of the CAPS-5 interviews. The participant will also be assigned another assessor at subsequent follow-ups. After each assessment, the assessors will be asked to guess the participants’ allocation, and answers will be compared to chance at the end of the study to measure blinding integrity. Data managers, primary outcome assessors and trial statisticians will be blinded to group allocation until the final data analyses are completed.

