#### Procedure for unblinding if needed {17b}

Emergency unblinding will be implemented when deemed clinically necessary, for example, in situations where treatment decisions demand knowledge of the allocated intervention or when there is an unexpected occurrence of a serious adverse event.

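### Having masked CAPS-5 assessors question patients about adverse events creates an avoidable risk to assessor masking that the blinding section does not fully close

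*Protocol article*

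**What the plan says.** All places are in the protocol article.

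- **Who will be blinded {17a}.** On the clinical side, "The therapists and the participants in the trial cannot be blinded to treatment allocation due to the complex nature of the treatment", whereas "group allocation will be masked to the assessors up to completion of the 12-month follow-up". The section also states: "Data managers, primary outcome assessors and trial statisticians will be blinded to group allocation until the final data analyses are completed". Its safeguards begin with an instruction: "Participants will receive explicit instructions not to discuss their treatment allocation with the assessor". If a participant nevertheless lets the arm slip, "another blind assessor will reassess the diagnosis and symptom severity using recordings of the CAPS-5 interviews", and a different assessor takes the later visits. Assessors guess the arm after each assessment, and the guesses are compared with chance at the end of the study.
- **Adverse event reporting and harms {22}.** Participants may report undesirable effects of treatment at any time "by alerting the designated therapist or assessor or contacting the study personnel". The next sentence sets the task: "The therapist and assessor will be instructed to ask follow-up questions about the intensity, duration, and characteristics of the adverse event". Separately, therapists and assessors must notify the study team at once if they fear serious harm to the participant or others.
- **Procedure for unblinding if needed {17b}.** Emergency unblinding is conditional on clinical necessity. The examples given are "in situations where treatment decisions demand knowledge of the allocated intervention or when there is an unexpected occurrence of a serious adverse event".

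**The concern.** The CAPS-5 total is rated by an interviewer, and Trial design {8} defines single-blind as masking of the assessors. If an assessor learns or guesses the arm before scoring, nothing else in the design protects that rating from expectation.

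The blinding section tries to keep treatment out of the conversation between participant and assessor. The harms section puts treatment effects into it and asks the assessor to probe. Participants who report adverse events are not a random subset. A leak through this route could therefore be related to outcome, and it could differ between arms if the kind or frequency of events differs. The documents do not show that it would.

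**Working it through.** No arithmetic applies. The article gives no adverse-event rate, no disclosure rate and no expected guess rate. The check is to set the sections side by side.

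1. **Can an answer reveal the arm?** Intervention description {11a} gives iPE as five days in a row, about 7 hours a day, with nine individual and five group sessions, followed by three boosters. Weekly PE is 15 individual 90-minute sessions with homework. Only one arm has group sessions or a treatment week. A participant who describes what an event was like, or what set it off, can mention one of these without naming an arm.

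2. **When does the assessor meet the participant?** Table 3 places CAPS-5 at enrollment and at 1, 6 and 12 months. The first scheduled assessor contact after allocation is therefore the primary-endpoint visit. The harms section does not say whether adverse-event questions come before or after the CAPS-5 rating, or whether they fall inside the recorded interview.

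3. **Do the safeguards in {17a} cover this route?**
   - *Instruction to participants:* it concerns discussing allocation. A participant answering a question about an adverse event need not see the answer as doing so.
   - *Re-rating and a new assessor:* both start from unintentional disclosure by the participant. A plain slip in reply to an adverse-event question is reasonably covered. An arm that the assessor works out from indirect cues is not expressly covered.
   - *Re-rating from the recording:* if the exchange was recorded, the second assessor may hear the same cue. The section does not say that such material is removed.
   - *Allocation guess:* this can show a loss of masking after the event but does not prevent it.

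4. **Is the assessor needed for this task?** Outcomes {12} has an open-ended adverse-event question at each treatment session and the self-rated NEQ from treatment completion onward. The harms section also names the therapist and study personnel as contacts. Detailed probing by the masked assessor is one of several routes.

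5. **Who could be unblinded under {17b}?** Therapists and participants already know the arm. The groups listed as masked are assessors, data managers and statisticians. {17b} does not say who receives the allocation or that these groups stay masked.

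**The case against.** The strongest reply is that {17a} already deals with exposure. A participant who answers an adverse-event question by mentioning a group session has unintentionally disclosed the arm, and re-rating and reassignment follow. The listed questions do not ask about allocation or format, and duration means how long an event lasted, not when it began. The article also promises, under Challenges, trial-specific routines to improve blinding integrity, which may be set out in documents not shown here. Much of this stands. It makes the problem a residual risk. It does not cover inference without disclosure or a cue left on the recording, and asking about characteristics is open enough to draw one out.

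A second objection is that judging urgency may itself require asking how severe an event is. That also stands, and it is why the assessor's duty to act on risk of harm should not be narrowed.

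Three stronger readings are tempting, and the documents do not support them.

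- *That the safety procedures do unmask the assessors.* The text creates an opportunity. It does not show that masking is lost.
- *That any serious adverse event triggers unblinding of the assessors.* {17b} requires clinical necessity, gives an unexpected serious event only as an example, and nowhere says that assessors are told.
- *That everyone giving care already knows the arm, so {17b} protects no one.* {17a} names only therapists and participants as unblinded. Other clinicians, such as the one who telephones after a PHQ-9 alert, may not know it.

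**Conclusion.** The point holds as an avoidable risk to the masking of the primary outcome that the protocol's own safeguards cover only in part. It rests on the wording of {22} and {17a} and on the visible difference between the two formats. It assumes that some participants will raise adverse events with the assessor and that some answers will carry a cue to the format.

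Its size cannot be worked out from the documents. A reader might take the 126 participants left after 10% attrition (140 × 0.9), assume that 10% to 30% report an event to the assessor and that half of the answers reveal the format, and arrive at about 6 to 19 exposed ratings (126 × 0.10 × 0.5 = 6.3; 126 × 0.30 × 0.5 = 18.9). Both rates would be invented, and nothing would be deducted for the re-rating in {17a}. That range is not evidence of magnitude.

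The silence of {17b} on who is told the allocation is a secondary matter of clarification. The change is worth making because it is cheap and protects the primary outcome.

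**What to change.** 1. In {22}, give follow-up questioning on non-urgent adverse events to the therapist or an unmasked coordinator. Alternatively, let the assessor ask only after the CAPS-5 score is locked and off the CAPS-5 recording. Participants may still report an event to an assessor, who notes it and passes it on.
2. Leave the assessor's immediate duty on risk of harm exactly as it is.
3. In {17a}, extend re-rating and reassignment to any loss of masking, including an arm inferred by the assessor or learned through a safety report. Make sure the re-rater does not hear the revealing exchange.
4. Reconcile {17b} with {17a}: state that the allocation goes only to those who need it for care, and that outcome assessors, data managers and statisticians stay masked.

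The cost is protocol and assessor-instruction wording, using existing staff and contact routes. The downside is a short delay while a non-urgent event is passed on. Reporting routes and the structured capture of harms are unchanged.

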### Frequency and plans for auditing trial conduct {23}

A + Science will perform regular audits during the trial. Potential changes in the protocol that arise will be described in detail on the Open Science Framework (OSF) and Clinicaltrials.org, and if needed, an amendment will be submitted to the Swedish Ethical Review Authority.

### Plans for communicating important protocol amendments to relevant parties (e.g., trial participants, ethical committees) {25}

If needed, amendments to the Swedish Ethical Review Authority will be submitted.

### Dissemination plans {31a}

Participants in a previous pilot study (manuscript in preparation) on intensive treatment were interviewed about their experiences, and some modifications were made to the treatment protocol accordingly. The findings in the trial will have important clinical implications for the treatment of PTSD and are of relevance to afflicted individuals, policy makers, clinicians, stakeholders, media, and the public. The results will be published in open access, scientific journals and by presenting the results at several national and international key conferences. The results will further be communicated more widely with help from the communication department at Karolinska Institutet and Region Stockholm. Since regular health care is already involved in the project, implementation is expected to be straightforward.

## Discussion

The study is the first trial to directly compare an intensive treatment for PTSD with first-line individual PE delivered for 15 weekly sessions in a Swedish psychiatric setting. The study is well powered as a superiority trial. If iPE are superior or comparable in terms of clinical efficacy and come with a lower dropout rate as well as faster recovery, it should be considered a candidate for implementation in regular care.

### Strengths of the study

The research group is highly experienced in trauma and PTSD research and in conducting randomized controlled trials. The therapists and assessors used in the trial received thorough training and supervision in the treatments investigated and the clinical gold-standard measure used to assess PTSD, respectively. Recruitment conducted in a Swedish psychiatric setting will provide valuable insights that can be applicable to routine psychiatric outpatient care.

### Challenges

The trial will be conducted in a publicly funded psychiatric outpatient setting in Stockholm, Sweden. From an implementation perspective, that is a great advantage. The major possible problem we can identify is therapist retention. The therapists delivering the treatment are employed by the county and typically have high caseloads to start with. Taking part in the trial is an additional responsibility that could be perceived as burdensome.

If a therapist or an assessor needs to terminate their engagement in the study, it can take some time first to find a replacer and train them in the treatment and in the CAPS-5.

The study also has some limitations. Therapists and participants will not be blinded to the allocated treatment arm. Blinded assessors will be used, and routines to improve blinding integrity will be developed specifically for this trial. Several measures to increase the overall scientific trustworthiness of the trial have been taken. The study hypotheses and the data analytic plan were prospectively registered. The chosen outcome measures for the study are considered the gold standard.

## Trial status

Inclusion started 12th of September 2023 and is expected to end in September 2025. The last follow-up appointment is expected to take place in October 2026. Data analysis and reporting of results will begin when all data from the primary endpoint have been collected (October 2025). Date and version identifier of the current study protocol: 2024–02-16 v 2.0.

## Data Availability

The principal investigator [name] will serve as the data custodian. Deidentified datasets can be obtained from the principal investigator upon reasonable request and under formal data transfer agreements to facilitate additional research.

## Abbreviations

AQoL-6D: Assessing Quality of Life 6 Dimensions
CAPS-5: Clinician-Administered PTSD Scale for DSM-5
CBT: Cognitive behavioral therapy
CEQ: Credibility/Expectancy Questionnaire
CHEERS: Consolidated Health Economic Evaluation Reporting Standards
CONSORT: Consolidated Standards of Reporting Trials
DSM-5: Diagnostic and Statistical Manual of Mental Disorders, fifth edition
GCP: Good Clinical Practice
IPE: Intensive prolonged exposure
ITQ: The International Trauma Questionnaire
NEQ: Negative Effects Questionnaire
RCT: Randomized controlled trial
SUD: Subjective Units of Distress Scale
TIC-P: Treatment Inventory of Costs in Psychiatric Patients
PHQ-9: Patient Health Questionnaire
PTSD: Post-traumatic stress disorder
WAI-SR: Working Alliance Inventory–Short Form Revised
